# Efficacy of an internet and SMS-based integrated smoking cessation and alcohol intervention for smoking cessation in young people: study protocol of a two-arm cluster randomised controlled trial

**DOI:** 10.1186/1471-2458-14-1140

**Published:** 2014-11-05

**Keywords:** Tobacco, Smoking cessation, Alcohol, Young people, Internet, Mobile phone

## Abstract

**Background:**

Tobacco smoking prevalence continues to be high, particularly among adolescents and young adults with lower educational levels, and is therefore a serious public health problem. Tobacco smoking and problem drinking often co-occur and relapses after successful smoking cessation are often associated with alcohol use. This study aims at testing the efficacy of an integrated smoking cessation and alcohol intervention by comparing it to a smoking cessation only intervention for young people, delivered via the Internet and mobile phone.

**Methods/Design:**

A two-arm cluster-randomised controlled trial with one follow-up assessment after 6 months will be conducted. Participants in the integrated intervention group will: (1) receive individually tailored web-based feedback on their drinking behaviour based on age and gender norms, (2) receive individually tailored mobile phone text messages to promote drinking within low-risk limits over a 3-month period, (3) receive individually tailored mobile phone text messages to support smoking cessation for 3 months, and (4) be offered the option of registering for a more intensive program that provides strategies for smoking cessation centred around a self-defined quit date. Participants in the smoking cessation only intervention group will only receive components (3) and (4). Study participants will be 1350 students who smoke tobacco daily/occasionally, from vocational schools in Switzerland. Main outcome criteria are 7-day point prevalence smoking abstinence and cigarette consumption assessed at the 6-month follow up.

**Discussion:**

This is the first study testing a fully automated intervention for smoking cessation that simultaneously addresses alcohol use and interrelations between tobacco and alcohol use. The integrated intervention can be easily implemented in various settings and could be used with large groups of young people in a cost-effective way.

**Trial registration:**

Current Controlled Trials ISRCTN02427446 (date of registration: 08th September, 2014).

## Background

Tobacco use is a major contributor to the global burden of disease [1]. Although smoking prevalence among young people in developed countries has been falling over the last two decades, smoking prevalence rates among 15- and 16-year-old adolescents in Europe, at approximately 28%, continues to be a serious problem, particularly among those with lower education levels [2].

Evidence on the effectiveness of smoking cessation interventions for young people is limited. The 2013 Cochrane Review of smoking cessation interventions for those younger than 20 years identified 28 substantial trials, of which only 3 were statistically significant [3]. The authors concluded that there is insufficient evidence to recommend the implementation of any one intervention model and that there continues to be a need for well-designed, adequately powered, randomized controlled trials.

The Internet and mobile phones are extremely popular among adolescents and young adults and are potential media for delivering smoking cessation support to large proportions of the population. In 2012, 95% of 12- to-19-year-old Swiss adolescents owned a mobile phone and 89% used the Internet daily or several times per week. Mobile phone use was the most frequent leisure time activity, while texting was the most frequent activity when using a mobile phone [4].

Expert system technology that provides information based on individual demographic- or smoking-related characteristics can be a viable time- and cost-saving alternative to interpersonal counselling [5]. Short message service (SMS) provides an opportunity for individualized and interactive information delivery that may be accessed easily, independent of time and place. A Cochrane Review on five randomized and quasi-randomized studies revealed overall long-term benefits of mobile phone interventions for smoking cessation among adults; however, a high level of statistical heterogeneity in the pooled results was found [6]. A recent meta-analysis investigating SMS-based health promotion interventions confirmed its efficacy and revealed that tailoring and personalizing messages was significantly associated with greater intervention effectiveness [7].

To date, two randomized controlled trials tested the efficacy of SMS-based programs for smoking cessation in young people aged 16–25 years [8, 9]. To test the *Stop My Smoking USA* program, 164 daily smokers, aged 18–25 years who seriously considered quitting were recruited through an online advertisement and were randomly assigned to either the 6-week intervention program or a matched control group for improving sleep and physical activity [9]. Intervention content was tailored to the participant’s stage within the quitting process. The intervention group received four messages per day during the pre-quitting stage for 2 weeks; in the quitting stage, they received four to nine text messages per day. The intervention significantly affected self-reported quitting rates at 4 weeks, but not at 3 months post-quitting. However, this study was not adequately powered to detect differences in quitting rates between the study groups at follow-up.

To test the efficacy of the *SMS-COACH* program, 755 vocational school students who were smoking regularly were randomly assigned to an intervention group or an assessment-only control group according to clusters based on their class. Within the online assessment, participants of the intervention group received questions that assessed outcome expectancies of smoking cessation, typical situations or circumstances in which cravings for cigarettes occur, and alternative strategies to handle these situations. During the 3-month intervention period, participants received one text message per week to assess smoking-related target behaviours. The stage of change combining smoking status and intention to quit according to the Health Action Process Approach (HAPA) [10] was assessed every alternate week. During the other weeks, the number of cigarettes smoked per day/week was assessed in the ‘pre-intention’ stages; in the ‘intention’ or ‘action’ stage, smokers were asked whether they applied individually selected strategies to cope with craving situations. Two feedback messages per week were tailored to the HAPA stages, baseline data, and weekly SMS assessments. The 7-day smoking abstinence rate at the 6-month follow-up was 12.5% in the intervention group and 9.6% in the control group. This difference was not statistically significant; however, the decrease in the mean number of cigarettes smoked per day from baseline to follow-up was significantly greater in the intervention group than in the control group.

To conclude, both studies on text messaging interventions for smoking cessation in young people showed promising results, however, they did not result in higher abstinence rates, suggesting that improving intervention efficacy is a major challenge. The provision of an integrated smoking cessation and alcohol intervention may be a promising approach for improving its effectiveness. Alcohol consumption and tobacco smoking often co-occur. Further, hazardous drinking is highly prevalent in adolescent and young adult smokers. A study conducted on vocational school students revealed that while 81% of smokers drank hazardously, only 49% of non-smokers drank hazardously [11]. Moreover, drinking alcohol increases cigarette cravings, and relapses after successful smoking cessation are often associated with alcohol consumption [12, 13]. This was also confirmed for adolescent smokers [14], suggesting that drinking alcohol during smoking cessation was strongly associated with the first lapse and subsequent intermittent smoking after quitting.

A pilot study on 41 participants testing an integrated smoking cessation and binge drinking intervention for young adult smokers with regular binge drinking revealed higher tobacco abstinence rates in participants receiving the integrated intervention than in those receiving standard smoking cessation treatment (36% vs. 21% at end of treatment at week 12) [15]. A similar pilot study that included 95 young adults, revealed abstinence rates of 21% vs. 9% at the end of treatment [16]. However, in both pilot studies, the differences between the groups were not statistically significant using the α =5% standard.

In the present study protocol, we describe a cluster-randomised trial comparing the efficacy of an optimized version of the former program *SMS-COACH*, now called *MobileCoach Tobacco (MCT)*, a text message-based smoking cessation program for young adults, to an extended program called *MobileCoach Tobacco + (MCT+),* a combined web- and text messaging-based integrated smoking cessation and alcohol intervention. This is the first study to compare an integrated smoking cessation and alcohol intervention to a smoking cessation only intervention within an adequately powered randomized controlled trial. Moreover, this is the first study to test the efficacy of an automated integrated smoking cessation and alcohol intervention for smoking cessation.

## Methods and design

### Design and hypotheses

A two-arm cluster-randomised trial will be conducted to test the efficacy of the *MCT*, a text messaging-based intervention for smoking cessation for young people compared to the *MCT+*, a combined web- and text messaging-based integrated smoking cessation and alcohol intervention. Study participants will be assessed at the baseline and at a 6-month follow-up (Figure 1). Our main hypothesis is that the integrated intervention will be more effective than the smoking cessation only intervention for reducing cigarette consumption and achieving smoking abstinence.

**Figure 1 Fig1:**
[figure not shown]
**Study design.**

### Participants, setting, and procedure

The interventions will be tested on vocational school students due to the high smoking prevalence in this population (approximately 42% of the Swiss sample were daily or occasional tobacco smokers) [11]. The Cantonal Office for Secondary Education in Zurich and further prevention specialist centres in other Swiss Cantons will request teachers from vocational schools to allow researchers to conduct the Internet- and text messaging-based smoking cessation program with some of their students. Participating teachers will schedule 30 minutes per class for eligibility screening, obtaining informed consent, and collect baseline data.

Study assistants (graduate students of psychology or prevention specialists) will recruit study participants by inviting all vocational school students from a school class to participate in an online health survey during a regular school lesson. Furthermore, they will inform students that some would be invited to participate in a study testing the efficacy of a text messaging intervention for health promotion. To decrease reporting bias, the study assistants will not provide further information about the purpose of the study until the completion of the eligibility screening. This online screening includes data collection on demographics, alcohol consumption, weekly physical activity, smoking status, and mobile phone ownership. Inclusion criteria are: (1) daily or occasional cigarette smoking (at least 4 cigarettes in the preceding month and at least one cigarette during the preceding week) and (2) ownership of a mobile phone.

Subsequently, study assistants will provide the eligible candidates with information about the study aims, interventions, assessments, reimbursement, and data protection, both online and in paper form. Reimbursement of 10 Swiss Francs (~ € 8.00) for participation at the 6-month follow-up assessment will be offered to all study participants. Moreover, participants will be offered 0.5 Swiss Franc (~ € 0.40) for responding to each of the 11 weekly SMS assessments conducted during the program. After obtaining informed consent online, all study participants will be requested to choose a username and provide their mobile phone number. Furthermore, the following smoking related variables will be assessed: intention to quit, daily/weekly cigarette consumption, previous cessation attempts, number of friends who smoke, age at smoking onset, smoking cessation outcome expectancies, situations in which craving for cigarettes occur, alternative strategies to handle these craving situations, and cost per pack of cigarettes. The integrated smoking cessation and alcohol intervention participants will receive additional questions on typical drinking days and times that are necessary for tailoring the intervention content. Computer assisted telephone interviews will be conducted by trained interviewers at the 6-month follow-up assessment.

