#### Text messages to support smoking cessation (MCT + and MCT)

During the 3-month intervention period, participants in both intervention groups will receive one text message prompt per week that either assesses smoking-related target behaviours or encourages participation in a quiz or a message contest. These prompts can be answered easily by typing a single letter, number, or a sentence using the mobile phone’s reply function. The weekly SMS prompt will be sent at a fixed time each week (Tuesday at 6 pm). The content of the prompt will depend on the individual HAPA stage as well as the number of the intervention week (odd or even).

Smoking-related target behaviour includes the HAPA stage, assessed every 4 weeks by responses to the question: ‘Have you recently smoked cigarettes?’, with the following response options (1) ‘Yes, and I do not intend to quit’ (pre-intender), (2) ‘Yes, but I am considering quitting’ (pre-intender), (3) ‘Yes, but I seriously intend to quit’ (intender), or (4) ‘No, I quit smoking’ (actor). Furthermore, among pre-intenders, we assess the number of cigarettes smoked per day or week (depending on smoking status: daily/occasionally), every 4 weeks, while for intenders and actors, we assess whether the individually chosen strategies to cope with craving situations, assessed within the baseline assessment, were applied, e.g. ‘Did you apply the following strategy recently? When I am at a party, I distract myself from smoking by dancing. Yes (Y) No (N)’.

Participants will receive an immediate feedback SMS after their response on the prompts regarding smoking-related target behaviours, e.g. ‘You can be really proud of yourself! Since the last assessment, you’ve smoked about 4 cigarettes less per day. That means you’re on the right path towards an active and healthy lifestyle.’

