### Outcomes

The primary outcome measures assessed at the 6-months follow-up are: (1) 7-day point prevalence smoking abstinence (i.e. not having smoked a puff within the past 7 days), (2) cigarette consumption (number of cigarettes smoked on a typical day for daily smokers, typical number of smoking days per month, and number of cigarettes smoked on a typical smoking day for occasional smokers).

Secondary outcome measures, assessed at the 6-months follow-up include: (1) 30-day point prevalence smoking abstinence (i.e. not having smoked a puff within the past 30 days), (2) stage of change according to the HAPA [10], (3) a quit attempt within the 6-month period, (4) alcohol consumption assessed by a 7-day drinking calendar, for which participants would need to think about a typical week in the month prior to assessment and recall the number of standard drinks they typically consumed for each day.

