### Data analyses

We will use regression models to compare the efficacy of the interventions on the different outcome measures. If necessary, we will control for baseline differences by entering additional baseline variables as covariates to the regression models. All analyses will be performed considering the intention-to-treat principle. Given the clustered nature of the data (students in different classes), we will compute robust variance estimators for all regression analyses.

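### For occasional smokers, the baseline cigarette measure as described does not match the 6-month primary outcome in unit, recall period or structure; the arm comparison stays unbiased and the precision cost is probably modest

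*Protocol article*

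**What the plan says.** The hypothesis in Design and hypotheses is that the integrated programme will be "more effective than the smoking cessation only intervention for reducing cigarette consumption and achieving smoking abstinence". Cigarette consumption is accordingly one of two primary outcomes.

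- **Baseline.** Participants, setting, and procedure lists the variables taken after consent, among them "intention to quit, daily/weekly cigarette consumption, previous cessation attempts". No other consumption item is listed there. The earlier eligibility screening covers smoking status and applies count thresholds (at least 4 cigarettes in the past month and at least one in the past week).
- **During the programme.** The section on text messages to support smoking cessation pairs unit with status: for pre-intenders, "we assess the number of cigarettes smoked per day or week (depending on smoking status: daily/occasionally".
- **At 6 months.** Outcomes defines "cigarette consumption (number of cigarettes smoked on a typical day for daily smokers", and, for the others, "typical number of smoking days per month, and number of cigarettes smoked on a typical smoking day for occasional smokers".
- **Analysis.** Data analyses plans regression models with robust variance for clustering. On baseline values it says: "If necessary, we will control for baseline differences by entering additional baseline variables as covariates to the regression models". No covariate is named, and no change score is specified.

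**The concern.** An occasional smoker appears to give a weekly total at baseline, and a frequency plus an amount per smoking day at follow-up. A weekly total cannot be split into days and amount afterwards, so an analysis plan written later could not recover the missing items.

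This matters for two reasons. First, the hypothesis speaks of reducing consumption, and the positive result of the predecessor trial described in the Background was a larger fall in mean cigarettes per day from baseline to follow-up. Readers will want the same description here. For occasional smokers it could not be given for smoking days or for cigarettes per smoking day. Second, baseline consumption is an obvious covariate for 6-month consumption. A covariate measured with a different question may predict the outcome less well, which would give up some precision on a primary outcome.

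**Working it through.** **1. The plan's own figures.** No standard deviation, baseline correlation or sample size is stated for cigarette consumption, so there is no consumption figure to reproduce. The stated sample size concerns abstinence (12% vs 18%, 80% power, two-sided 5%). The pooled two-proportion formula gives 555 per arm, and with continuity correction 588, as stated. The design effect is 1 + (4 − 1) × 0.05 = 1.15, and 588 × 1.15 = 676.2 against the stated 675. Nothing in this point changes those figures.

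**2. Measures side by side.**

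| | Baseline | 6 months |
|---|---|---|
| Daily smokers | cigarettes per day | cigarettes on a typical day |
| Occasional smokers | cigarettes per week (inferred) | smoking days per month; cigarettes per smoking day |

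Daily smokers match. Occasional smokers do not.

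**3. What can be converted.** With 365.25 / 12 / 7 ≈ 4.35 weeks per month, the follow-up total is

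cigarettes per week = days per month × cigarettes per smoking day / 4.35.

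A baseline for total amount therefore exists. The reverse split into days and amount does not.

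**4. Why conversion can be noisy (illustration, values assumed).** Someone smokes 4 cigarettes on each of 3 days a month, so 12 per month. If the baseline item refers to the past week and that week held one smoking day, they report 4, which converts to 4 × 4.35 ≈ 17 per month. Consumption would seem to fall from 17 to 12 with no change in behaviour. This applies in both arms alike, so it adds noise to the comparison and not bias. If the item asks about a typical week, the problem is smaller; the article does not say which.

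**5. Precision, under assumptions.** With baseline adjustment, residual variance is proportional to 1 − ρ², where ρ is the correlation of baseline with follow-up. Let ρ be the value with matched items and kρ the value with the mismatched item. The variance ratio among those affected is (1 − k²ρ²) / (1 − ρ²).

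| ρ (assumed) | k = 1 | k = 0.9 | k = 0.8 | k = 0.7 |
|---|---|---|---|---|
| 0.5 | 1.00 | 1.06 | 1.12 | 1.17 |
| 0.6 | 1.00 | 1.11 | 1.20 | 1.29 |
| 0.7 | 1.00 | 1.18 | 1.35 | 1.49 |

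Only occasional smokers are affected. If they are a share s of participants, with equal variances assumed, the overall ratio at ρ = 0.6 and k = 0.8 (kρ = 0.48) is

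[(1 − s) × 0.64 + s × 0.7696] / 0.64 = 1 + 0.2025 s.

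- s = 0.2: 1.04
- s = 0.5: 1.10

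If conversion loses no correlation (k = 1), the ratio is 1.00. If occasional smokers had no usable baseline at all, it would be 1 + 0.5625 s, that is 1.11 to 1.28 over the same shares. Step 3 shows that this extreme does not apply.

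**The case against.** The strongest reply is that the mismatch is inferred. The baseline phrase is one entry in a condensed list, the questionnaire is not shown, and the pairing of week with occasional smokers comes from the description of SMS prompts, where a single number suits the reply format. This stands as a caution. It is why the fix allows for the questionnaire already containing the right items. The same day/week pairing in two places still makes the inference the natural reading.

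Second, the primary outcomes are defined at 6 months and compared by regression. No change score is planned, nor any split into days and amount, and reduced consumption can be tested as a difference between arms at follow-up. That also stands: the planned comparison is valid without a matched baseline.

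Third, the precision loss depends on adjusting for baseline consumption, which the article makes conditional, and the size of any loss follows entirely from assumed correlations. This stands too, and it limits what can be claimed.

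Fourth, baseline is online and follow-up is by telephone, so the same wording would not make the two measurements identical. True, but the mode difference applies to every participant; the change of question is a separate and avoidable source of mismatch.

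A reader might go further and infer that this primary outcome has no comparable baseline at all, or that precision is certainly lost. The document supports neither. Daily smokers have the same unit at both times, and the occasional smokers' total can be converted. One qualification: daily smokers match while they remain daily, and Outcomes does not say whether baseline or follow-up status decides which items a person is asked.

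**Conclusion.** The point holds for occasional smokers only. Their baseline measure, as described and with the weekly unit inferred, differs from their 6-month primary outcome in unit, recall period and structure. The contrast between arms stays unbiased because both arms are measured the same way, and no stated power figure is affected.

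The certain consequence is descriptive: if the inference is right, change in smoking days and in cigarettes per smoking day cannot be derived for this group. The consequence for precision is probably modest and possibly nil. At a matched correlation of 0.6, weakened to 80% of its value, with 20% to 50% occasional smokers and equal variances, overall residual variance rises by 4% to 10%; with lossless conversion it rises by 0%. The correlations, the weakening and the share are all assumptions, so these figures show scale and are not estimates. The case for acting rests on the low cost of the remedy, not on a large demonstrated loss.

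**What to change.** 1. At the online baseline, ask occasional smokers the two items from Outcomes, with the same wording: typical smoking days per month and cigarettes on a typical smoking day. They can replace the weekly count or sit beside it. If the questionnaire already asks them, correct the baseline list in Participants, setting, and procedure, and the measurement part of the point is closed.
2. In Data analyses, name baseline consumption as a fixed covariate in the consumption model, in place of the conditional rule, and state the common unit in which it enters (for example, cigarettes per month).

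The cost is one or two extra online questions for occasional smokers within the 30 minutes scheduled per class, plus edits to two sections. If recruitment has begun, classes already assessed would keep the weekly item, converted to the common unit; their days and amount at baseline cannot be recovered.
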